## Abstract

Resuscitative endovascular balloon occlusion of the aorta (REBOA) is a method to provide temporary control of noncompressible torso hemorrhage in trauma patients. Previous research on REBOA has mainly focused on animals and patients. This study aims to explore whether thigh cuff inflation combined with simulated hemorrhage can serve as an experimental human model for zone 3 REBOA. Lower body negative pressure is a model of hypovolemia. A zone 3 REBOA occludes aorta at its bifurcation, essentially excluding the pelvis and lower extremities from the circulation. Bilateral proximal thigh cuffs will occlude blood vessels to and from the lower extremities. Twenty healthy volunteers will be exposed to bilateral proximal thigh cuff inflation to suprasystolic pressures to simulate the hemodynamic effects of REBOA during experimental hemorrhage using lower body negative pressure (LBNP). Each participant will complete two experimental conditions in a randomized order within one study visit. In the one condition, subjects will undergo only 60 mmHg LBNP for six minutes. In the alternate condition, 60 mmHg LBNP will be applied for six minutes, adding thigh cuff inflation during the final three minutes. Continuous, non-invasive monitoring of systemic hemodynamic parameters—including arterial blood pressure, stroke volume, and heart rate—will be conducted. Cerebral hemodynamics will be assessed by measuring middle cerebral artery blood velocity and cerebral oxygenation. Pain related to thigh cuff inflation will be assessed using a verbal numerical rating scale. The impact of thigh cuff inflation on systemic and cerebral hemodynamics will be evaluated using mixed-effects regression modeling. This study aims to examine the systemic and cerebral hemodynamic effects of combined thigh cuff inflation and lower body negative pressure in healthy volunteers. Based on the feasibility and findings, the potential of this combination as a model for zone 3 REBOA in simulated hemorrhage will be discussed.

## Introduction

Among patients under the age of 45 years, trauma is the leading cause of death [1], with the majority of deaths occurring in the prehospital phase [2]. In both civilian and military settings, noncompressible torso hemorrhage (NCTH) represents the majority of potentially preventable trauma deaths [3,4]. Further treatment options are needed to improve the pre- and in-hospital survival of patients with NCTH.

Resuscitative endovascular balloon occlusion of the aorta (REBOA) is a method used in NCTH and hemorrhagic shock as a temporary measure before definitive hemorrhagic control can be achieved [5]. In REBOA, a balloon is inflated in the descending aorta, occluding blood flow and preventing further hemorrhage distal to the occlusion. The balloon can be positioned in three different zones in the descending aorta, depending on the location of the bleeding. Occlusion distal to the renal arteries is designated as zone 3 [6]. Since the introduction of REBOA in the 1960s, the method has more recently also been applied in the prehospital setting [7,8].

REBOA has profound hemodynamic effects [9]. Cardiac afterload and arterial blood pressure increase, potentially elevating cerebral perfusion pressure [10,11]. In addition to systemic hemodynamic effects, it is relevant to investigate cerebral hemodynamic effects, as polytrauma patients may suffer from traumatic brain injury (TBI). Using REBOA in these situations might increase the risk of intracranial hemorrhage and elevate intracranial pressure, potentially worsening patient outcomes. [12,13]. Although REBOA has demonstrated significant hemodynamic effects in animal and surgical settings, there remains a need for non-invasive, human experimental models to understand its physiological impact in awake individuals [14].

Lower body negative pressure (LBNP) is a model used to simulate hemorrhage in awake, healthy volunteers. Negative pressure is applied to the lower body, causing pooling of venous blood in the lower extremities and pelvis. Consequently, venous return and cardiac stroke volume are reduced, similar to what is observed during hemorrhage [15]. In contrast, arterial occlusion of the lower limbs has been shown to temporarily increase MAP, HR and systemic vascular resistance (SVR) [16]. Thigh cuff inflation achieves this arterial occlusion by restricting blood flow to the lower extremities and may therefore replicate some of the hemodynamic effects associated with zone 3 REBOA [17]. One previous study reported that a higher LBNP intensity was required to elicit similar reductions in stroke volume when arterial occlusion was combined with LBNP, compared to LBNP alone [18]. However, in that study, arterial occlusion was induced using tourniquets applied before, rather than during, LBNP.

Whether combining thigh cuff inflation and LBNP is a feasible method to investigate the hemodynamic effects of zone 3 REBOA during hemorrhage in healthy volunteers remains to be studied. The aim of this study is to investigate the systemic and cerebral hemodynamic effects of thigh cuff inflation during LBNP in healthy volunteers. The primary hypothesis is that thigh cuff inflation will affect cardiac stroke volume during LBNP. The secondary hypothesis is that thigh cuff inflation will affect the response in mean arterial blood pressure (MAP) and middle cerebral artery velocity (MCAV) during LBNP.

## Materials and methods

### Study design

This is an ongoing, single-center, experimental study with a randomized, controlled crossover design. Subject recruitment began on April 4, 2024, and is anticipated to finish by February 28, 2025, with results expected by December 1, 2025. Each subject will undergo two experimental conditions in a randomized order during a single visit. In the one condition, 60 mmHg of LBNP will be applied for six minutes. In the other condition, 60 mmHg of LBNP will be applied for six minutes, with thigh cuff inflation added during the final three minutes [19]. A washout period of at least 20 minutes between the two conditions will be applied to minimize potential carry-over effects. Furthermore, any bias introduced by a possible residual carry-over effect is minimized by the randomized study design.

The experimental protocol is illustrated in **Fig 1**. Before the experiment begins, the subject will rest in the supine position for at least 20 minutes to stabilize hemodynamic parameters. Manual arterial blood pressure will be measured using a brachial cuff, and heart rate will be measured by ECG to define the LBNP stop criteria. After five minutes without LBNP, a 60 mmHg LBNP will be applied for six minutes, either with or without the addition of inflated thigh cuffs for the final three minutes. Following 20 minutes of supine rest, another five minutes of registration without LBNP followed by six minutes of 60 mmHg LBNP will be applied. During the second LBNP exposure, the opposite thigh cuff intervention will be used, ensuring that all subjects are exposed to LBNP both with and without inflated thigh cuffs (crossover).

**Fig 1 pone.0327404.g001:**
[figure not shown]
Illustration of the experimental protocol. The subject will participate in two experimental conditions. In randomized order, the subject will participate in one condition including lower body negative pressure (LBNP) 60 mmHg for six minutes and another experimental condition with both LBNP 60 mmHg for six minutes and thigh cuff inflation for the last three minutes.

LBNP will be terminated after completing six minutes of 60 mmHg, or earlier if the subject exhibits symptoms of impending hemodynamic decompensation such as blurred vision, lightheadedness, dizziness, nausea or sweating. Objective stop criteria for early termination include a reduction in heart rate or MAP to less than 75% of baseline that lasts more than three seconds. Additionally, LBNP will be terminated at the subject’s request for any reason other than those mentioned above.

### Subjects

Healthy volunteers will be included based on the eligibility criteria listed in **Table 1**. The subjects must refrain from caffeine (six hours), alcohol (24 hours) and strenuous exercise (on the test day) prior to the visit. They may eat a light meal up until two hours before the visit. A thorough introduction to the experimental setup will be provided before the subject gives written and oral consent to participate in the study. Each subject will receive a universal gift card of 500 NOK (approximately €43) to compensate for the inconvenience and discomfort of participating in the study.

**Table 1 pone.0327404.t001:** Eligibility criteria for the study population.

• Age between 18 and 50 years • No illnesses or health conditions that cause functional limitations in daily life or that require regular medication (except contraception or medication for allergies) • Normal physical performance (e.g., able to walk and climb stairs without discomfort) • No unexplained fainting episodes (previously assumed vasovagal syncope with a presumed known trigger, such as blood sampling, is acceptable) • Not pregnant

### Randomization

The subjects will be randomized in a ratio of 1:1 to begin the test session with one of the two experimental conditions: LBNP alone or LBNP combined with thigh cuff inflation. To ensure an approximately equal number of subjects beginning the test session with either experimental condition, we will use block randomization with blocks of four or eight using the “blockrand” package in R [20]. Allocation will be concealed using sealed, opaque envelopes with sequential allocations, prepared in advance by a person otherwise not involved in the study. This will ensure that group assignment will remain unknown to the enrolling investigator until start of the experiment.

### Interventions

#### Lower body negative pressure.

The subjects will be positioned in the supine position with deflated thigh cuffs. A saddle will be placed between the legs to minimize the use of leg muscles and prevent activation of the muscle-vein pump. The chamber will be air-sealed at the level of the iliac crest. The room temperature will be maintained between 22 and 24 °C. The model is illustrated in **Fig 2**.

**Fig 2 pone.0327404.g002:**
[figure not shown]
Illustration showing the subject with thigh cuffs inside the LBNP chamber. 1) The lower body negative pressure (LBNP) chamber is 2) sealed just above the iliac crest and connected to 3) a vacuum pump controlled by 4) a pressure control unit. The applied negative pressure is displayed on 5) a pressure monitor. 6) Thigh cuffs are positioned proximal on both thighs, inflated by 7) Venopulse. 8) The pulse oximeter is positioned at the first toe on the left foot, ensuring complete occlusion to the lower limbs. Measuring 9) ascending aortic blood velocity by suprasternal pulsed Doppler ultrasound, 10) ECG, 11) mean arterial pressure (MAP) on 12) a data acquisition device, 13) sampled continuously on a laptop. 14) Cerebral tissue oxygen saturation (ScO2) will be measured by near-infrared spectroscopy sampled on 15) an Invos monitor. 16) Mean cerebral artery velocity is sampled by a 1-5 MHz M5S probe connected to 17) Triplex transcranial Doppler ultrasound.

#### Thigh cuffs.

To approximate the hemodynamic effects of zone 3 REBOA, bilateral thigh cuffs will be positioned proximally on the thighs and inflated to a suprasystolic pressure during LBNP, as described in **Fig 2**. The thigh cuffs will be inflated to 80 mmHg above systolic blood pressure, as indicated by the manual arterial blood pressure measured at rest before LBNP. To minimize discomfort, we will use contoured thigh cuffs (CC22, 24x122.5cm cuff size Hokanson, Bellevue, WA, United States) with careful attention to finding the best and most comfortable placement as proximally as possible on the thighs. The thigh cuffs will be inflated rapidly using a Rapid Cuff Inflation device connected to Venopulse (STR Teknikk, Ålesund, Norway). Arterial occlusion will be confirmed by the disappearance of photoplethysmographic pulsation from a pulse oximeter placed on the first toe of the left foot.

### Measurements and data processing

Ascending aortic blood velocity will be measured using suprasternal pulsed Doppler ultrasound, with a 2 MHz probe (SD-50; Vingmed Ultrasound, Horten, Norway). Stroke volume will be calculated as the product of the aortic blood velocity-time integral and the left ventricular outflow tract (LVOT) area. The diameter of the LVOT will be measured with echocardiography in the parasternal long-axis (1–5 MHz M5S probe, Vivid E95; GE Vingmed, Horten, Norway) [21], and the area will be calculated assuming a circular LVOT. The heart rate will be calculated from a three-lead ECG (Bio Amp/PowerLab, AD Instruments, Bella Vista, Australia). Cardiac output will be calculated as the product of heart rate and stroke volume.

The arterial blood pressure waveform will be measured continuously and noninvasively using the volume clamp method on the third finger of the left hand (Human NIBP Nano System; Finapres Medical System B.V., Netherlands). End-tidal CO_2_ (ETCO_2_) will be measured with sidestream capnography (Medlab CAP 10; Medlab GmbH, Stutensee, Germany). The photoplethysmography (PPG) waveform from the first toe on the left foot will be obtained using a pulse oximeter (Masimo Radical 7; Masimo Corp, CA, USA).

We will measure MCAV using triplex transcranial Doppler (TCD) ultrasound with a 1–5 MHz M5S probe (Vivid E95). The probe will be positioned over the right anterior temporal window and the middle cerebral artery (MCA) will be identified by its characteristic shape, depth (25–50 mm), and blood flow direction [22]. The sample volume will be placed to obtain a clear Doppler signal with a minimal insonation angle. The probe position and ultrasound machine settings, including the sample volume and angle will not change during both experimental conditions within each subject. The same operator will perform all TCD measurements to ensure reliability and uniformity in data collection. Cerebral tissue oxygen saturation (ScO_2_) will be obtained using near-infrared spectroscopy (Invos 5100C cerebral/somatic oximeter; Somanetics, Troy, MI, USA).

Pain will be registered using a verbal numerical rating scale (VNRS), ranging from 0 (no pain) to 10 (worst imaginable pain). To minimize psychomotor and biofeedback responses during the protocol, subjects will be asked to rate their pain once after completing both conditions. As pain was not a predefined endpoint, we will conduct a post hoc analysis of these data.

Stroke volume, heart rate, cardiac output, MAP, ETCO_2_ and PPG waveform will be sampled at 1000 Hz using Lab Chart 8.1.28 (ADInstruments, Bella Vista, Australia). MCAV recordings will be exported as AVI-files to Cardiovascular Suite 4.0 (Quipu, Pisa, Italy) for Doppler waveform analysis to calculate the time-averaged maximum velocity. To synchronize the timing of the TCD recordings with the other recorded signals, the recordings will be mirrored directly into Lab Chart 8.1.28 via Digital Visual Interface (DVI) using a video grabber. ScO_2_ data will be exported as.txt-files. Analyses will be performed in R [23] using RStudio [24].

### Outcomes

The primary outcome is the effect of thigh cuff inflation on stroke volume during LBNP. The secondary outcomes are the effects of thigh cuff inflation on MAP and MCAV during LBNP.

### Statistical methods

#### Sample size.

We have previously observed a mean (standard deviation) reduction in stroke volume of 44 (11) % during 60 mmHg compared to zero mmHg of LBNP [25]. Based on these assumptions, simulations in R have shown that a sample size of 16 subjects will detect a 10% difference between the experimental conditions with α = 0.05 and (1-β)=0.90. To account for potential dropouts, we plan to enroll 20 subjects.

#### Statistical analyses.

Due to the repetitive nature of the data and the clustering within subjects, the predefined primary and secondary hypotheses will be evaluated using mixed regression models, with subjects as a random effect. The details in the models (e.g., covariance structures and the use of generalized additive mixed models) will depend on the residual distribution and linearity of the data.

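### The analysis names subject as the only random effect for repeated within-exposure data; fitted as a subject intercept, it would give intervals that are too narrow because the exposure (subject-by-condition) level is missing

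*Protocol article*

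**What the plan says.** Under Statistical analyses, the article gives its reason for a mixed model, "Due to the repetitive nature of the data and the clustering within subjects", and then says that the hypotheses "will be evaluated using mixed regression models, with subjects as a random effect". No other random effect is named. The rest is left open: "The details in the models (e.g., covariance structures and the use of generalized additive mixed models) will depend on the residual distribution" and on linearity.

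Under Study design, "Each subject will undergo two experimental conditions in a randomized order during a single visit". One condition is LBNP alone. The other is LBNP "with thigh cuff inflation added during the final three minutes". Each subject therefore supplies one exposure per condition.

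Under Measurements and data processing, stroke volume and MAP are among the signals that "will be sampled at 1000 Hz using Lab Chart 8.1.28". The article does not say whether the analysed row is a beat, a second, an epoch or an exposure mean.

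**The concern.** The data have three levels: values within an exposure, exposures within a subject, and subjects. The cuff is allocated at the middle level, with two exposures per subject. A subject intercept removes stable differences between people. It does not remove the difference that one person shows between two exposures for reasons unrelated to the average cuff effect. The article itself gives reasons to expect such variation: possible residual carry-over (Study design) and a sympathetic response to cuff pain (Methodological considerations).

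Without a term for the middle level, that variation enters the residual as if it were independent from row to row, and the standard error shrinks as rows are added. The criteria that are to settle the model details do not test for the missing component: residuals can look normal and the time course linear while it is absent. The primary test on stroke volume and both secondary tests (MAP and MCAV) share this structure, so the stated alpha of 0.05 is at stake in all three.

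**Working it through.** **1. The plan's own figure.** Inputs from Sample size: SD 11 points, difference 10%, alpha 0.05 (two-sided assumed), power 0.90. The SD of the paired difference is not given; taking it as 11 means a within-subject correlation of 0.5.

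- Normal approximation: (1.960 + 1.282)² × (11/10)² = 10.51 × 1.21 = 12.7, so 13 subjects.
- Paired t-test: 15 subjects; power at 16 is 92.4%. Exactly 90% at 16 corresponds to an SD of the difference of about 11.5.

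So 16 is reproduced closely on a subject-level, paired reading.

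**2. Set-up for the model check.** No cuff effect; direct comparison of the two conditions over the cuff window; n = 20 subjects; m values per exposure. Assumed, because the article does not give them: residual SD σw = 8 points; exposure SD σe from 2 to 7.8 points, where 7.8 = 11/√2 corresponds to a true between-condition difference with SD 11; m = 3, 18 or 180 (1-minute, 10-second or 1-second values in three minutes).

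**3. Formulas (balanced data, independent residuals).**

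- True variance of the estimated difference: (2/n)(σe² + σw²/m).
- Residual variance estimated by the subject-intercept model: s² = [2n(m−1)σw² + (n−1)(mσe² + σw²)] / [n(2m−1) − 1].
- Variance that the model reports: 2s²/(nm).
- Type I error: 2Φ(−1.96 × reported SE / true SE).

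**4. One case in full: m = 18, σe = 7.8 (σe² = 60.5).**

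- s² = [2×20×17×64 + 19×(18×60.5 + 64)] / 699 = (43,520 + 21,907)/699 = 93.6.
- Reported SE = √(2×93.6/360) = 0.721.
- True SE = √[0.1 × (60.5 + 3.56)] = 2.531, which is 3.51 times larger.
- Type I error = 2Φ(−1.96/3.51) = 2Φ(−0.558) = 58%.
- 95% interval width: 2×1.96×0.721 = 2.8 points reported, against 2×2.093×2.531 = 10.6 points for the paired analysis with 19 degrees of freedom.

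**5. All cases from the same formulas.**

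| Values per exposure | σe = 0 | σe = 2 | σe = 7.8 | True/reported SE, σe = 2 to 7.8 |
|---|---|---|---|---|
| 3 | 5% | 7% | 21% | 1.1 to 1.6 |
| 18 | 5% | 17% | 58% | 1.4 to 3.5 |
| 180 | 5% | 57% | 86% | 3.5 to 10.9 |

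Simulation of this set-up, with lag-1 residual correlation of 0 or 0.5, gives roughly 8-29%, 17-59% and 58-87% for σe from 2 to 7.8. A paired test on exposure means gives about 3-6%. A fitted mixed model (16 subjects, 18 values, 100 runs, SD of the condition difference 11) rejected in 61% of runs with the subject intercept only and in 5% with a subject-by-condition term.

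**6. Does serial correlation alone cure it?** No. With 16 subjects, 180 values and lag-1 correlation 0.9, a subject intercept plus AR(1) residuals gave type I error of about 38% (SD of the condition difference 11) and 30% (SD 5.5), but about 8% when that SD was 0.

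**7. Is a zero exposure SD plausible?** With independent residuals and σe = 0, the paired difference would have SD 8√(2/m): 6.5, 2.7 or 0.8 points for m = 3, 18 or 180. Ten points at 90% power would then need 7, 4 or 3 subjects. The article's 16 fits an SD near 11.5, so on a paired reading its planning already implies substantial variation at the exposure level.

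**The case against.** The article names a grouping factor, not a finished model. A random condition slope by subject fits its wording and, with two conditions, is essentially the missing term. Covariance structures are expressly left open, and an analysis plan that is not shown may settle them. All of that stands.

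The row unit is also not fixed: 1000 Hz is an acquisition rate. That stands too. Still, one mean per exposure leaves two rows per subject and no time curve, which sits poorly with the mention of linearity and generalized additive mixed models. Several rows per exposure is the natural reading, and inflation already appears with three.

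The contrast matters as well. If the model tests the change from the pre-cuff LBNP phase between conditions, a constant exposure offset cancels; simulated type I error was then about 1-5% with independent residuals. Inflation returns if the change itself varies between exposures (2-60% for an SD of 3 points) or if serial correlation is ignored (4-27% at correlation 0.5).

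Finally, the SD of 11 in the article describes the fall from zero to 60 mmHg LBNP, not the difference between two exposures. Its use for the upper value of 7.8 is an assumption.

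**Conclusion.** The point holds conditionally. The only random effect named is at the wrong level to carry the cuff comparison by itself, and the stated criteria for choosing model details would not bring in the right one. If a subject intercept is fitted to several values per exposure and conditions are compared directly, the intervals are too narrow unless exposures differ by no more than independent residual noise. The size runs from slight (about 7-8% type I error with three values and an exposure SD of 2) to severe (above 80% with 180 values and an exposure SD of 7.8). It rests on the assumed SDs, row counts and contrast.

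A reader might infer that the plan does analyse beats or seconds as replicates, or that its error rate is certainly far above 5%. The article supports neither, because it does not state intercept-only, the row unit or the contrast. Nor does the point show the sample size of 16 to be wrong. The variation at issue is between two exposures within one visit, not between visits.

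**What to change.** In Statistical analyses, state the analysed row and the tested contrast, and then one of the following:

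- **Mixed model:** add a subject-by-condition random effect (equivalently, a random condition slope by subject), with serial residual correlation when several values per exposure are modelled. If the contrast is condition by phase, let that change vary by subject.
- **Summary analysis:** compute one cuff-window summary per subject per condition, or its change from the pre-cuff LBNP phase, and test the conditions as pairs.

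Add that this structure stays whatever the residual checks show; those checks may still guide the shape of the time curve. The change costs a sentence and a small amount of code. Intervals become wider, but correct: in the worked case about 10.6 points instead of 2.8.
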